
## Methods

### Study design

This project is designed as a longitudinal prospective, multi-design study, incorporating both a randomised controlled study (for intervention and sedentary participants) and a non-randomised controlled study (for intervention/sedentary and regular active participants). The study will utilise between-group (intervention, sedentary and active participants) and within-subject measures (baseline, post-intervention and 1- to 12-month follow-ups) (see Fig. 1). The Intention-to-treat methodology, considered the gold standard for RCTs [69, 70], will be implemented to ensure that data from the participants in each assessment phase fit with the inclusion criteria of each study group, with the aim of preventing interferences caused by unexpected changes over time in their assigned condition (e.g., an active women withdraws regular practice due to injury; or a sedentary woman is motivated to autonomously become an exerciser). Moreover, this approach will help to mitigate the potential reduction sample size and loss of statistical power resulting from participant attrition.

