### Participants and eligibility criteria

The participants will be 300 postmenopausal women aged 45 to 65 years living in Granada, a city in the South of Spain with a population of > 230,000, as of 2023 [73]. Participants will be recruited using non-probabilistic, convenience procedures (see Procedure section).

Inclusion criteria will be: 1) being postmenopausal women between 45 and 65 years old; 2) with no menses for 12 months or more and up to 10 years after menopause, i.e., early postmenopause based on Stages of Reproductive Ageing Workshop STRAW + 10 criteria [74]; 3) able to speak and read Spanish with proficiency; and 4) able to provide informed consent for voluntary participation. Additionally, inclusion criteria for the intervention/sedentary control groups are: a) being sedentary (having not engaged in moderate-to-vigorous exercise on a regular basis, independent of daily physical activity, e.g., walking for transportation) for at least the 12 months prior to the beginning of the study, as screened with the self-report described below; b) able to exercise, i.e., in good health that allows them to exercise, based on medical criteria (see below); and c) willingness to be randomised to intervention/non-intervention (waiting list) conditions. For the active control group, these criteria are: i) exercising on a regular basis reaching international recommended levels for health promotion for at least the last 12 months, as screened with the self-report described below. In addition, exclusion criteria are: 1) use of hormone therapy in the three months before recruitment; and 2) suffering from any physical or mental disease that would seriously deteriorate functioning, impede participation in exercise based on medical criteria or introduce bias in responses. For the active participants, an athlete (i.e., competitive sport) of any performance level will be excluded. Selection criteria will be examined after recruitment to check eligibility and proceed with the study group assignment.

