### Procedures

The study will be publicised through several channels (e.g., media advertisements, online social networks, institutional e-mailing, gynaecology outpatient clinics, women’s associations, gyms, fitness clubs, community and university exercise programmes, neighbourhood associations, other community resources, snowball sampling) to recruit a wide sample of postmenopausal women interested in participating, along with information on how to contact the researchers (an e-mail and a telephone number). Once potential participants contact the research staff, they will be required to attend an informative session where they will receive detailed information about the general goal and procedures of the study, their rights and tasks as participants and topics such as the confidentiality of their responses and the exclusive use of data for scientific purposes. During this meeting, participants will be encouraged to express any doubts or concerns and to consult with the research staff. After agreeing to continue with enrolment, participants will be asked to sign an informed consent form. A research assistant will then contact each participant to schedule two lab visits for the first assessment phase, which will include a face-to-face clinical interview, the self-report-based evaluation conducted through an online survey implemented using an open access resource such as Limesurvey (Limesurvey GmbH, Hamburg, Germany) [95] and the remaining measures that need to be completed (e.g., weight, fitness tests). Baseline measurement will be conducted with all the women to screen eligibility criteria and collect pre-intervention data.

Upon meeting the eligibility criteria, the final study sample will be allocated to an intervention group receiving the intervention (*n* = 100), a control group of sedentary women (*n* = 100) and a control group of regularly active women (*n* = 100). The non-active participants will be randomly allocated to two groups: the intervention group and the sedentary control group, making this a randomised controlled arm of the study. This random allocation will be performed by, for example, computer-generated random numbers. The sedentary control group will be considered a waiting list group. On the other hand, women who already engage in regular exercise will be assigned to the active control group. Since these women are already active, this will be a non-randomised controlled arm of the study.

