
During the interventions described in 1) and 2), attendance to the exercise programme will be monitored by the trainer. Regular updates will be provided to the participants by the researchers and will serve as a basis for working with the behavioural change intervention.

3)A health education and promotion intervention (15 60-to-90 min. sessions) designed and implemented by experts in women’s health, will also be offered. This will focus on providing information and recommendations regarding a healthy lifestyle during postmenopause. The issues covered will include healthy eating and weight management, sexuality and intimate relationships, family and social support, social activities, emotional self-regulation, body appearance management and body image, unhealthy habits such as tobacco and alcohol use and other health-related behaviours (e.g., sleep, leisure time habits). This intervention will also be offered on a voluntary basis to the participants in the control groups to ensure equal treatment among the study groups in terms of lifestyle after menopause (except for active behaviour). Health education is typically provided as standard care in menopause and postmenopause (e.g., EMAS Consensus Statement [82].

After the multi-component intervention, measurements will be repeated at post-intervention and follow ups. All the measurements will be conducted to ensure that the evaluators are blinded to the participants’ allocation to the study groups (e.g., online survey). 

To encourage adherence to the procedures, various strategies will be implemented, including the provision of regular feedback on attendance to the exercise programme and sending reminders to participants regarding the assessment phases. Additionally, in cases of non-compliance, motivational inquiry will be conducted through open and supportive dialogue to address the underlying reasons and to ensure compliance. Nevertheless, disengagement can offer interesting information, and the non-adherent participants will not be excluded from the study or analyses. 

Figure 1 illustrates the stages, planning and distribution of the research activity as well as the flow of the current study procedures. The timeline of the procedure is described as a SPIRIT figure in Fig. 2.

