Ethical approval has been obtained from the Ethics Committee on Human Research of the University of Granada (Spain), reg. B-CTS-342-UGR20 (2021–23), on November 17, 2021. Written informed consent will be obtained from all the participants. All procedures will be conducted in accordance with the ethical principles for research involving human subjects detailed in the Declaration of Helsinki and updates. Study participation will be voluntary. Reasons for withdrawal may include exercise-related injuries, significant changes in health status, hormone therapy recommendation or the participant’s personal request to withdraw or refuse consent at any time during the study.

The study protocol has been pre-registered at BMC ISRCTN registry (ISRCTN16251361).

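### The rule labelled intention-to-treat is worded as a check of each assessment's data against group inclusion criteria; applied as written, it would bias the randomised comparison towards the intervention

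*Protocol article*

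**What the plan says.** Under Study design, the protocol article adopts ITT and explains its purpose. It "will be implemented to ensure that data from the participants in each assessment phase fit with the inclusion criteria of each study group". The reason offered for this condition is prevention: the article imposes it "with the aim of preventing interferences caused by unexpected changes over time in their assigned condition". Two examples follow: an active woman who stops because of injury, and the case in which "a sedentary woman is motivated to autonomously become an exerciser". The next sentence adds that "this approach will help to mitigate the potential reduction sample size and loss of statistical power resulting from participant attrition".

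Four other places bear on this:

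- **Procedures** sets the randomised contrast: "The non-active participants will be randomly allocated to two groups: the intervention group and the sedentary control group".
- **Participants and eligibility criteria** makes "being sedentary (having not engaged in moderate-to-vigorous exercise on a regular basis" an entry condition for both randomised arms, referring to at least the 12 months before the study.
- **Intervention** says of disengagement that "the non-adherent participants will not be excluded from the study or analyses".
- **Data management and analyses** lists exercise behaviour and the HAPA constructs as primary outcomes. It treats missing data by pairwise deletion, or by last observation carried forward (LOCF) where appropriate, with follow-up data from controls as the example.

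**The concern.** ITT means that women are analysed in the arm to which they were randomised, whatever they do afterwards. The description in Study design points the other way: at each assessment the data are to match the status that defines the group. A control who starts exercising no longer matches, and her starting is an outcome of the trial. Any rule that takes her observed data out of the control arm removes a control with a good result because the result was good. The control mean falls, and the difference moves towards the intervention even when the intervention does nothing.

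Such take-up is plausible. The controls volunteered, accepted possible allocation to an exercise programme and are on a waiting list, and the article itself names the case. What is at stake is the only randomised comparison in the study, for exercise behaviour and for the volitional constructs in H3. H1 (change within the intervention group) and H2 (a baseline comparison) are not affected by screening controls after baseline.

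**Working it through.** **The text set side by side**

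1. Label: ITT, with data kept as allocated. Description: data at each assessment fit the inclusion criteria. The two cannot both be followed once a woman's status changes.
2. Stated benefit: less loss of sample size. A status screen can only keep or reduce the number analysed; retention as allocated is what protects it.
3. Being sedentary is an entry criterion for both randomised arms. Taken as a condition on current status, it would also fail for intervention women in whom the programme works, so the rule cannot be applied coherently.
4. The Intervention section keeps non-adherent women. If this covers every participant, it conflicts with the screen. If it covers only women who leave the programme, it says nothing about controls. The article does not settle which.

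**The plan's own figure**

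The sample size paragraph gives 80 evaluable women per group and 20% dropout: 80 / (1 − 0.20) = 100 enrolled per group, as stated. I use 80 per arm below.

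**Illustration 1: control starters deleted (assumed inputs)**

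The documents give no uptake rate, gain or SD. Assume no true effect, a share p of each arm taking up exercise unprompted, a gain of 600 MET-min/week, and noise SD s. Starters are deleted from the control arm only.

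- Intervention mean gain = 600p; remaining control mean gain = 0; spurious difference = 600p.
- Control n = 80(1 − p).
- SE² = [s² + 600²p(1 − p)] / 80 + s² / [80(1 − p)].
- One-sided false-positive rate = P(Z > 1.96 − difference/SE); nominal 0.025.

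At p = 0.20 the difference is 0.20 × 600 = 120, control n is 64, and 600² × 0.16 = 57,600.

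- s = 400: SE² = 217,600/80 + 160,000/64 = 2,720 + 2,500, SE = 72.2; 120/72.2 = 1.66; rate 0.38.
- s = 1000: SE² = 1,057,600/80 + 1,000,000/64 = 13,220 + 15,625, SE = 169.8; 120/169.8 = 0.71; rate 0.10 to 0.11.

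| Uptake p | Spurious difference (MET-min/week) | Control n | Rate, s = 400 | s = 600 | s = 1000 |
|---|---|---|---|---|---|
| 10% | 60 | 72 | 0.14 | 0.09 | 0.06 |
| 20% | 120 | 64 | 0.38 | 0.21 | 0.10 |
| 30% | 180 | 56 | 0.66 | 0.38 | 0.17 |

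A Monte Carlo run with Welch tests at 20% uptake gave 0.37, 0.21 and 0.11.

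**Illustration 2: other ways of making the data fit**

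Here the outcome has SD 1, and starting to exercise has an assumed correlation ρ of 0.3 to 0.8 with the control's outcome. With φ the normal density at the (1 − p) quantile:

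- Deletion: bias = ρφ/(1 − p). At p = 0.10, φ = 0.1755, giving 0.06 to 0.16 SD. At p = 0.20, φ = 0.280, giving 0.10 to 0.28 SD.
- Reassignment to the active group: the randomised contrast is the same as under deletion.
- Replacement by the baseline value (LOCF), with an assumed baseline-to-follow-up correlation of 0.6: bias = (1 − 0.6)ρφ, giving 0.02 to 0.06 SD at p = 0.10 and 0.03 to 0.09 SD at p = 0.20.

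With all women analysed as allocated, the simulated difference under no effect was 0.00.

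**The case against.** The strongest reply is that no exclusion is stated. The section calls ITT the standard for randomised trials, refers to the assigned condition, and expects sample size to be protected, which deletion could not do. The sentence may be a garbled way of saying that women stay in their assigned group despite later changes. In addition, the sedentary criterion concerns the 12 months before the study, so read literally no later behaviour can breach it.

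Much of this stands. It is not established that controls who start exercising will leave the analysis. But the stated aim and the sedentary example show that current status is in view, and a reader applying the sentence would have to do something with such a woman's data. If real ITT was meant, the sentence misdescribes it and needs the same correction.

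A reader might also infer an asymmetry: intervention women who stop are kept, while controls who start are removed. The article does not say so. That reading needs the retention statement to apply to the intervention arm alone, yet its paragraph opens with adherence to study procedures in general and may cover everyone. Nor does the list of reasons for withdrawal in the Intervention section support it: "Reasons for withdrawal may include exercise-related injuries, significant changes in health status, hormone therapy recommendation" describes why a woman might leave, not how data are selected.

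**Conclusion.** The sentence is wrong as a definition of ITT and should be corrected. It describes a condition on post-randomisation status that is bound up with a primary outcome, and it must be reconciled with the retention statement in the Intervention section. The bias is conditional: it arises if the sentence is applied by dropping, reassigning or replacing the data of controls who start exercising.

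Its direction is then towards the intervention wherever starters do better than other controls. Its size is not in the documents. Under the assumptions of 20% uptake in both arms, a 600 MET-min/week gain, no true effect and deletion in the control arm only, it is about 120 MET-min/week, with a one-sided false-positive rate of roughly 10% to 38% for noise SD 1000 to 400. LOCF replacement gives a smaller bias in the same direction. The stronger conclusion, that the plan does remove these controls, goes beyond the text.

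**What to change.** - Replace the sentence with: all randomised women are analysed in their allocated arm with all observed outcome data, whatever their later activity level.
- Delete the condition that data at each assessment fit the group inclusion criteria.
- Analyse active controls by their status at enrolment.
- Record changes of activity status, and use them only in a sensitivity analysis labelled per-protocol.
- Reword the retention statement in the Intervention section so that it plainly covers all groups and agrees with the new definition.

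This changes wording only and needs no new data. The cost is that the estimated effect may be smaller, because controls who take up exercise on their own count in the control arm.

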**Fig. 1 Fig1:**
[figure not shown]
Flowchart with the stages of the research activity and the recruitment and study group assignment

The SPIRIT recommendations for the design and implementation of interventional trials [71] were followed in the design of the project. The CONSORT guidelines for reporting RCTs will be observed for communicating the findings [72].

### Participants and eligibility criteria

The participants will be 300 postmenopausal women aged 45 to 65 years living in Granada, a city in the South of Spain with a population of > 230,000, as of 2023 [73]. Participants will be recruited using non-probabilistic, convenience procedures (see Procedure section).

Inclusion criteria will be: 1) being postmenopausal women between 45 and 65 years old; 2) with no menses for 12 months or more and up to 10 years after menopause, i.e., early postmenopause based on Stages of Reproductive Ageing Workshop STRAW + 10 criteria [74]; 3) able to speak and read Spanish with proficiency; and 4) able to provide informed consent for voluntary participation. Additionally, inclusion criteria for the intervention/sedentary control groups are: a) being sedentary (having not engaged in moderate-to-vigorous exercise on a regular basis, independent of daily physical activity, e.g., walking for transportation) for at least the 12 months prior to the beginning of the study, as screened with the self-report described below; b) able to exercise, i.e., in good health that allows them to exercise, based on medical criteria (see below); and c) willingness to be randomised to intervention/non-intervention (waiting list) conditions. For the active control group, these criteria are: i) exercising on a regular basis reaching international recommended levels for health promotion for at least the last 12 months, as screened with the self-report described below. In addition, exclusion criteria are: 1) use of hormone therapy in the three months before recruitment; and 2) suffering from any physical or mental disease that would seriously deteriorate functioning, impede participation in exercise based on medical criteria or introduce bias in responses. For the active participants, an athlete (i.e., competitive sport) of any performance level will be excluded. Selection criteria will be examined after recruitment to check eligibility and proceed with the study group assignment.

After enrolment, participants will be assigned to one of three study groups by randomisation and non-randomisation, depending on the study condition. The groups are as follows: 1) Intervention-initiators (participants who will engage in a supervised exercise programme complemented with a HAPA-based intervention, *n* = 100); 2) control-sedentary (non-active women who will maintain their sedentary lifestyle and will not receive any intervention for promoting behavioural change, *n* = 100) and 3) control-active (women with a regular and sustained exercise habit, *n* = 100).

The sample size has been calculated to include 80 participants per group, considering an *alpha* error of 0.05 and a *beta* error of 0.2, for independent groups and continuous variables, i.e. mean comparisons, with estimated mean values based on previously published studies [64, 65, 68], to ensure sufficient statistical power to detect a moderate treatment effect in a clinical study (Clincalc®). To account for potential dropouts, we anticipate a 20% dropout rate, increasing the sample size up to 100 participants per group. 

Figure 1 shows a flow chart of the study participants, including the selection process.

### Measures

Measurements will be taken at baseline, post-intervention and at 1-, 3-, 6- and 12-month follow-ups. This comprehensive assessment will enable the exploration of the factors that predict the initiation and maintenance of exercise behaviour, as well as the stages of the behaviour change process. 

#### Personal data (baseline)

Participants will complete a socio-demographic, clinical and lifestyle data form including information on age, educational level, employment status, occupation, average household income, marital status, number of children, family caring roles and current major stressful life events.

Moreover, the participants’ personal medical history will be obtained through clinical interviews conducted by the gynaecologists collaborating with the research team [75]. Information will be gathered on: a) Gynaecological antecedents including age at menarche, main features of menstrual cycles (e.g., regularity, dysmenorrhea), age at final menstrual period, time since menopause, obstetric history on gravidity and parity (GTPAL, G = gravidity, T = term deliveries, P = preterm deliveries, A = abortions or miscarriages, L = live births), age at first and last pregnancy and natural lactation; b) life-course, recent (last 12 months) and current gynaecological and general main diseases and surgeries, recent (last 12 months) and current drug treatments (particularly corticosteroids), previous and current use of hormone therapy, previous bone fractures and previous bone densitometries; c) regular gynaecological (breast and pelvic) screenings and hormone blood tests; and d) family history (especially bone fractures, cardiovascular diseases and gynaecological cancers).

Lifestyle will be explored through an *ad-hoc* self-report survey on health-related behaviours in key areas of women’s health. These areas include physical activity and exercise, nutrition, sleep, leisure, substance use (e.g., alcohol use and smoking), sexual relationships, emotional self-regulation, social relationships and support, self-protection (e.g., sun protection), health responsibility (e.g., regular medical screenings) and life appreciation and self-actualisation (e.g., life satisfaction, meaning and purpose in life) based on previous questionnaires [76].

#### Active behaviour (all assessments)

Active lifestyle will be assessed with the short form of the International Physical Activity Questionnaire (IPAQ) [77], Spanish version [78]. The IPAQ is a widely used self-report instrument for assessing physical activities that people carry out as part of their daily routines. These include activities related to transportation, occupation, household chores and recreation. This questionnaire enables the estimation of total light, moderate and vigorous physical activity and exercise, as well as the amount of time spent sitting during the last seven days. The data gathered using the IPAQ can be used to determine indicators of volume of physical activity and energy expenditure (e.g., METs-min/week). These indicators can then be compared against recommended levels of healthy activity. The psychometric properties of the IPAQ have been demonstrated in the Spanish population [78, 79]. The information collected with the IPAQ at baseline will be used to assign the participants to the study groups, as well as to assess activity levels throughout the study.

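### Groups are defined by 12 months of regular exercise but assigned with a seven-day questionnaire of all physical activity, which can establish neither the exercise history nor exercise apart from daily activity

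*Protocol article*

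**What the plan says.** Under Participants and eligibility criteria, women for the intervention and sedentary groups must have done no regular moderate-to-vigorous exercise, "independent of daily physical activity, e.g., walking for transportation) for at least the 12 months prior to the beginning of the study". Active controls must have been "exercising on a regular basis reaching international recommended levels for health promotion for at least the last 12 months". Both criteria are screened with a self-report that the section says is described later but does not name.

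Under Active behaviour (all assessments), the short-form IPAQ is described. Of the activities it records, the article says: "These include activities related to transportation, occupation, household chores and recreation". Its output is total activity by intensity, with exercise counted in. The recall period appears where sitting time is added: "as well as the amount of time spent sitting during the last seven days". The role in allocation is explicit: "The information collected with the IPAQ at baseline will be used to assign the participants to the study groups". The same form measures activity at every later assessment. Data management and analyses lists exercise behaviour, with the HAPA constructs, as primary outcomes compared across phases and groups.

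One other self-report touches on exercise: the ad-hoc lifestyle survey under Personal data (baseline). The article gives it neither a 12-month window nor a role in assignment.

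**The concern.** The assignment rule and the eligibility rule measure different things over different periods. A woman who does no planned exercise but has a physically demanding job or heavy housework can score as active. A regular exerciser in a week off can score as sedentary. Errors of either kind blur the comparison of active with non-active women, including the baseline comparison in H2.

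The second consequence comes from using one score twice. If women are sorted on a single noisy weekly value and change is then measured from that value, the low group tends to rise and the high group to fall at retest with no change in behaviour. On the IPAQ this could pass for improvement within the intervention group, or for convergence between new exercisers and active controls.

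**Working it through.** **Step 1: the two rules side by side.**

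| | Eligibility criteria | IPAQ, as the article describes it |
|---|---|---|
| What is classified | Regular exercise; for the sedentary criterion, daily activity is set aside | Activity in transport, work, household and recreation |
| Period | At least 12 months | Last seven days |
| Instrument | A self-report, not named | Short-form IPAQ, named as the tool for assignment |

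Both rows of substance disagree. Splitting the score by intensity does not separate planned exercise from daily activity, because moderate housework still counts as moderate activity. The Background suggests that the distinction matters here. It cites about two-thirds of middle-aged and older postmenopausal women in southern Spain reaching 300 minutes a week of healthy activity, and 75% of Spanish women aged 50 to 64 doing no vigorous exercise. The sources and intensities differ, so this is only suggestive.

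**Step 2: regression to the mean, as an illustration.** The plan gives no figure on this point and no reliability for the IPAQ, so every input is an assumption:
- a standardised score (mean 0, SD 1);
- groups cut at the median of the baseline score;
- selection on the IPAQ alone;
- test-retest correlation r from 0.8 down to 0.6.

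The mean of the lower half of a standard normal is −√(2/π) = −0.80, and of the upper half +0.80. At retest, with no change in behaviour, each group mean becomes r times its baseline value. The shift per group is therefore (1 − r) × 0.80, and the gap goes from 1.60 to r × 1.60.

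| r | Shift per group (SD) | Gap at retest (SD) |
|---|---|---|
| 0.8 | 0.2 × 0.80 = 0.16 | 1.28 |
| 0.7 | 0.3 × 0.80 = 0.24 | 1.12 |
| 0.6 | 0.4 × 0.80 = 0.32 | 0.96 |

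A simulation with 2,000,000 draws gives the same values. Widening r to 0.9 and 0.5 gives shifts of 0.08 and 0.40 SD.

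**Step 3: misclassification from weekly noise alone.** In the same simulation, the share of women whose observed score falls on the other side of the cut from their long-run level is 15%, 18% and 22% for r = 0.8, 0.7 and 0.6. Counting non-exercise activity would add to this. The documents do not allow that part to be estimated.

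**Step 4: the randomised contrast.** When the low group is split at random in two, the difference in change between the halves is 0.00 at every r. Both arms are selected in the same way and regress equally.

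**The case against.** The article says that IPAQ information will be used in assignment, not that it is used alone. The unnamed screening self-report could be the lifestyle survey, and Procedures adds a face-to-face clinical interview at baseline. Recruitment runs partly through gyms and exercise programmes. If a real 12-month screen operates, a regular exerciser in a week off would still fail the sedentary criterion. Groups that truly differ would also regress toward their own means rather than a common one. This stands as a limit on size: the shifts above assume selection on the IPAQ alone and lie toward the upper end. It does not remove the contradiction, because the only instrument given an assignment role is the IPAQ.

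Three stronger readings are tempting and not supported.
- A reader might infer that regression to the mean would mimic the results predicted by H1 and H3. Those hypotheses concern HAPA variables, which are affected only as far as they correlate with the selection score. The volitional constructs in H3 are listed only from post-intervention onward, so they have no baseline to regress from. H3 also requires a difference from sedentary women, and for the intervention arm that contrast is randomised.
- A reader might set the shift against the effect the trial is sized for. The article calls that effect only moderate and gives no mean or SD. It is also described as a treatment effect, and the randomised contrast that estimates it is not biased here.
- A reader might say the blinding claim is false because participants report their own outcomes. The article says "All the measurements will be conducted to ensure that the evaluators are blinded to the" group allocation. It claims blinding of evaluators only, and it already lists reliance on self-report as a limitation.

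**Conclusion.** The point holds as a contradiction between two stated rules. Groups are defined by at least 12 months of regular exercise, and assignment is given to a seven-day measure of all activity. Women can be misclassified in both directions; the documents do not show how many would be. Within-group IPAQ change and IPAQ comparisons with the non-randomised active controls are open to regression to the mean. The illustration is 0.16 to 0.32 SD per group, so 0.32 to 0.64 SD of apparent closing of the gap. It rests on an assumed test-retest correlation of 0.8 to 0.6, a median cut and selection on the IPAQ alone. The randomised intervention-versus-sedentary contrast is not biased by this; misclassification could at most dilute it. The rule should be corrected, but the main randomised comparison does not fall with it.

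**What to change.** Change the assignment sentence under Active behaviour so that eligibility and group assignment rest on 12-month planned-exercise items: type, frequency, duration and intensity, asked separately from daily activity. Add these items to the lifestyle survey under Personal data (baseline), and name that survey as the screening self-report in the eligibility section. Keep the IPAQ as the measure of activity over time, since the article cites Spanish psychometric support for it. Replacing it as an outcome with new, unvalidated items would be a trade-off that this point does not require.

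In the analysis section, base conclusions about change in exercise behaviour on the randomised intervention-versus-sedentary contrast. Treat within-group IPAQ change and convergence with active controls as descriptive.

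The cost is a few survey items, some recall error over 12 months, and a protocol amendment if enrolment has begun, which the retrospective registration suggests. Women already allocated cannot be reassigned.
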